### Statistical analysis

2.8

Efficacy will be assessed in the full analysis set (FAS) and the per-protocol (PP) set. The FAS will include all subjects who meet the inclusion/exclusion criteria, provide voluntary informed consent to participate in the study, receive at least 1 dose of the investigational product after randomization, have FMA assessment, that is, the primary efficacy endpoint, at screening, and at least once at weeks 4, 8, or 12 during the follow-up period. The PP set will include all FAS subjects who do not have any major violations such as major protocol violations (excluding minor violations) and have a primary efficacy assessment per protocol. Subjects with an overall medication compliance of <70% will be excluded from the PP set. Safety will be assessed in the safety set, which will comprise of all subjects who receive at least 1 dose of the investigational product after randomization.

The primary efficacy endpoint will be analyzed both in the FAS and the PP sets. The final conclusions of the study will be made based on the FAS results, in principle. Mean, SD, median, and range (minimum, maximum) of FMA motor score before dosing and 12 weeks after dosing, as well as score change between the 2 time points, will be presented for the high- and low-dose HT047, and the placebo groups. To assess intergroup differences in the primary endpoint, that is, FMA change, analysis of covariance, with baseline FMA as a covariate, and Tukey multiple comparison test will be carried out. Dunnett multiple comparison, which would consider the placebo group as a comparator group, will not be used because this phase 2 study aims to evaluate adequate dosage and therefore, will compare the HT047 high-dose group with the HT047 low-dose group.

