The secondary efficacy and exploratory endpoints will be also analyzed both in the FAS and the PP set, with the final conclusions to be made based on the PP set results. For each secondary efficacy and exploratory endpoint, mean, SD, median, and range (minimum, maximum) will be presented by the group for continuous data, whereas frequency and percentage will be provided by the group for categorical data. For the following secondary efficacy endpoints, generalized estimating equation analysis will be conducted for overall data or by subgroup, according to the relevant definition. For generalized estimating equation analysis, the following intergroup differences in FMA score change at each time point will be assessed by performing a contrast analysis, while a trend analysis will be conducted to characterize the trend in FMA change between time points by group: intergroup comparison of change in FMA motor score at weeks 4 and 8 from the baseline; intergroup comparison of FMA motor score change at weeks 4, 8, and 12 from the baseline according to the timing of treatment initiation after the onset of stroke (either within 1 week or 1–2 weeks), and according to the presence of prognostic risk factors (hypertension, diabetes, dyslipidemia, etc); intergroup comparison of change in K-NIHSS and K-mRS scores at weeks 4 and 12 from the baseline; and intergroup comparison of change in K-MBI score at weeks 4 and 12 from the baseline. For the following secondary efficacy endpoints, a Chi-squared test will be conducted, and if there is an intergroup difference in proportion, a Hochberg test will be carried out to compare the HT047 high-dose, HT047 low-dose, and placebo groups to control for multiplicity issues: intergroup comparison of the proportion of subjects with K-NIHSS score 0 to 2 at week 12; intergroup comparison of the proportion of subjects with K-mRS score 0 at week 12; intergroup comparison of the proportion of subjects with K-mRS score ≤1 at week 12; and intergroup comparison of the proportion of subjects with K-mRS score ≤2 at week 12. To assess intergroup difference in the exploratory endpoint, that is, change in MoCA-K score at week 12 from the baseline, analysis of covariance and Tukey multiple comparison test will be carried out.

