A comprehensive statistical analysis plan will be finalized prior to database locking. Details of statistical analyses that are not presented in the protocol will be described in the statistical analysis plan. All statistical analyses will be performed at a 2-sided significance level of 10%. To handle the missing data, the last observation carried forward method will be used for FMA motor score, the primary outcome variable. If FMA motor score is measured only at screening, substitution for missing data will not be performed. Similarly, for the other outcome variables, missing data will not be substituted and included in the statistical analysis. Interim analysis will not be performed.

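### The subgroup endpoints are tested by between-arm contrasts within each level at 10%, with no interaction test or multiplicity control stated, so they cannot show whether the effect differs and will produce chance findings

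*Protocol article*

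**What the plan says.** Section 2.6 of the protocol article lists FMA motor change at weeks 4, 8 and 12, split by timing of treatment start and by prognostic risk factor, among the secondary efficacy endpoints. Section 2.8 gives the method: "generalized estimating equation analysis will be conducted for overall data or by subgroup, according to the relevant definition". The test is also stated: "intergroup differences in FMA score change at each time point will be assessed by performing a contrast analysis". The subgroup comparisons are an "intergroup comparison of FMA motor score change at weeks 4, 8, and 12 from the baseline", split "according to the timing of treatment initiation after the onset of stroke (either within 1 week or 1–2 weeks") and also "according to the presence of prognostic risk factors (hypertension, diabetes, dyslipidemia, etc").

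On the error rate, section 2.8 says: "All statistical analyses will be performed at a 2-sided significance level of 10" percent. Conclusions on secondary endpoints are drawn from the PP set, with the FAS analysed as well.

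Multiplicity control is assigned endpoint by endpoint in section 2.8: Tukey for the primary endpoint and for MoCA-K, Hochberg for the responder proportions. None is named for the GEE contrasts. Section 2.7 sets aside type 1 error adjustment for the three-group comparison, except for the primary outcome.

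**The concern.** A split by timing or risk factor is useful mainly for learning whether the effect of HT047 depends on that factor. That is a question about the difference between two treatment effects, and an interaction term addresses it. A p-value below 0.10 in one level and above it in the other does not, because the two levels can easily fall on different sides of the threshold when the true effect is the same in both.

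A second and independent problem is the number of tests. Many contrasts at 10% without adjustment will give some nominally significant results even if neither dose does anything.

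The article says that a phase 3 trial will be planned from these results. A chance finding in, say, early starters or patients with diabetes could be taken for a real one at that stage.

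**Working it through.** **Inputs from the article.** Difference 14.5 points, SD 19.2, two-sided level 10%, power 80%, 22 evaluable and 26 enrolled per group (section 2.7). Visits at weeks 4, 8 and 12; timing in two levels; three named risk factors and an open list (section 2.8).

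**Inputs that are assumptions.** Each risk factor has two levels (present or absent). All three pairs of arms are contrasted; section 2.8 says the plan "will compare the HT047 high-dose group with the HT047 low-dose group" when it discusses the primary endpoint, and carrying this to the subgroup contrasts is an assumption. One analysis set is counted. Half of each arm falls in each level, that is 11 (of 22) to 13 (of 26).

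**The plan's own figure.** n = 2 × [19.2 × (1.645 + 0.842) / 14.5]² = 21.7, so 22 per group; 22 / 0.85 = 25.9, so 26. The stated sample size is reproduced.

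**Problem 1: significance in one level only.** The power of one pairwise contrast within a level is Φ(14.5 / (19.2 × √(2/n)) − 1.645).

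- n = 11: Φ(1.771 − 1.645) = 0.55
- n = 13: Φ(1.925 − 1.645) = 0.61

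The two levels contain different patients, so their results are independent. If the true effect is 14.5 points in both, the chance that exactly one is significant is 2p(1 − p):

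- n = 11: 2 × 0.55 × 0.45 = 0.50
- n = 13: 2 × 0.61 × 0.39 = 0.48

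An uneven split does not help. With 7 and 15 of 22 per arm, the powers are 0.41 and 0.66, and the chance is 0.41 × 0.34 + 0.66 × 0.59 = 0.53.

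**Problem 2: number of contrasts.** Count = factors × levels × visits × pairs. Expected false positives = count × 0.10 if neither dose has any effect. Correlation between contrasts does not change this expectation.

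| Assumption | Contrasts | Expected false positives |
|---|---|---|
| Four named factors, all pairs | 4 × 2 × 3 × 3 = 72 | 7.2 |
| Four factors, placebo pairs only | 4 × 2 × 3 × 2 = 48 | 4.8 |
| Five factors, all pairs | 90 | 9.0 |
| Six factors, all pairs | 108 | 10.8 |
| Four factors, all pairs, week 12 only | 24 | 2.4 |
| Four factors, all pairs, FAS and PP both counted | 144 | 14.4 |

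The first row was checked by simulation under no effect: 22 or 26 per arm, within-patient correlation of 0.8 and independent factors (all assumed), two-sample t tests in place of GEE contrasts, 4,000 runs per setting. The mean was 7.1 to 7.3 false positives, with a 5th to 95th percentile range of 0 to 19. The chance of at least one was about 0.93. The formula for independent tests, 1 − 0.9^72 = 0.9995, overstates this because the contrasts share patients.

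**With one week-12 interaction test per factor.** Four tests at 10% give 4 × 0.10 = 0.4 expected false positives. The chance of at least one is about 0.32 to 0.35 by simulation, in line with 1 − 0.9⁴ = 0.34.

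**The case against.** The strongest reply is that the article condenses a longer protocol and leaves unstated details to a SAP that is not shown. A reader might infer that no interaction test will be run. The article does not say so; it only states none. Nor does it say that significance in one level alone will be read as a differential effect. By-level contrasts from a single joint model would also fit its wording, so separate fits per level are the natural reading but not a certain one. All this stands, but it does not remove the point. The test that the article does state is the between-arm contrast by subgroup, and that contrast does not compare levels, whichever model it comes from.

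Several stronger readings are also unsupported:

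- The false positives do not result from the missing interaction test. They come from many unadjusted contrasts at 10%.
- The count of 72 is not a figure in the article, and about 7 is a mean. The contrasts are correlated, so false positives cluster: some trials would show none and others well over ten.
- A robust-variance z test in cells this small would exceed its nominal level; in the same simulation it raised the mean count to 9.4 to 10.1. The article specifies neither the variance estimator nor the reference distribution, so this cannot be charged to the plan.
- The article does not say that subgroup results will set phase 3 eligibility.

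Finally, this is an exploratory phase 2 trial, and its primary conclusion, from ANCOVA with Tukey in the FAS, is untouched. That limits the harm. It would be a full defence if the subgroup results were labelled descriptive, but they are secondary endpoints on which the plan says conclusions are drawn.

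**Conclusion.** The point holds as two separate weaknesses of a stated analysis.

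1. The within-level contrasts cannot show that the effect depends on timing or on a risk factor. At the plan's own effect size and SD, a uniform effect would be significant in exactly one level about half the time per pairwise contrast. This rests on an assumed even split; the uneven example gives much the same answer.
2. About 7 false positives are expected across the four named factors if neither dose works, with a chance of about 0.93 of at least one. Between placebo pairs only and six factors, the expected number runs from 4.8 to 10.8 per analysis set. It falls to 2.4 if only week 12 is counted.

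The article does not establish that an interaction test is excluded; it establishes only that none is stated. The matter deserves correction but does not threaten the primary analysis.

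**What to change.** For each factor, fit one GEE to all patients in the analysis set, in both FAS and PP as already planned, with treatment-by-factor-by-visit terms. Report the week-12 interaction test, and the treatment effect with its confidence interval in each level. Limit the factors to timing, hypertension, diabetes and dyslipidemia, and delete the open end of the list. State that within-level p-values are descriptive and support no conclusion.

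The cost is wording in the protocol and in the SAP, which is to be finalized before database lock. No new data are needed, and there is one model per factor where separate fits would need two. The drawback is that interaction tests have low power at this sample size, and four of them at 10% still carry about a one-in-three chance of a false positive. The subgroup results therefore remain exploratory and should be presented as such.

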### Eligibility criteria

2.2

The inclusion and exclusion criteria are provided in Table 1. Briefly, patients are eligible if they have had an ischemic stroke confirmed by brain imaging within 14 days of screening, are aged 19 years or older, have arm or leg weakness with a Fugl-Meyer assessment (FMA) motor score ≤55 at screening, and have a Korean version of the National Institutes of Health Stroke scale (K-NIHSS) score ≥4 and ≤15 at screening.

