### Randomization and blinding

2.5

Eligible participants will be randomly assigned to one of the following 3 groups in a 1:1:1 ratio: high-dose (750 mg 3 times a day), low-dose (500 mg 3 times a day), and placebo groups. An independent statistician will generate a list of random numbers using a centralized stratified block randomization method. Randomization will be stratified according to the hospital, so that all hospitals have a 1:1:1 ratio. The study drug and placebo will be sealed in sequentially numbered identical bottles according to the allocation sequence. Each participant will be assigned an order number and will receive the investigational product or placebo in the corresponding prepacked bottles. Participants and all research personnel will be blinded to the assignment. The randomization code will be kept secure by an independent statistician and can only be broken in the case of an emergency. If a code break occurs, the investigator will report the reason and procedures and the administration of investigational drug will be discontinued.

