### Outcome measures and endpoints

2.6

The Korean version of the FMA motor score will be used to measure the primary endpoint.^[19]^ The motor domain of FMA ranges from a score of 0 (flaccid hemiplegia) to 100 (normal movement), with 66 points for the upper limb and 34 points for the lower limb. An educated physiotherapist will perform all motor assessments at baseline and weeks 4, 8, and 12. The K-NIHSS and Korean versions of the modified Rankin scale (K-mRS), the modified Barthel index (K-mBI), and the montreal cognitive assessment (MoCA-K) will be used at baseline and weeks 4 and 12.

The primary efficacy endpoint is the change in FMA motor score at week 12 from the baseline. The secondary efficacy endpoints are: the change in FMA motor score at weeks 4 and 8 from the baseline; the change in FMA motor score at weeks 4, 8, and 12 from baseline according to the timing of treatment initiation after the onset of stroke (either within 1 week or 1–2 weeks) or according to the presence of prognostic risk factors (hypertension, diabetes, dyslipidemia, etc); the change in K-NIHSS and K-mRS scores at weeks 4 and 12 from the baseline; the proportion of subjects with a K-NIHSS score of 0 to 2 at week 12; the proportion of subjects with a K-mRS score of 0, ≤1, and ≤2 at week 12; and the change in K-MBI score at weeks 4 and 12 from the baseline. Exploratory endpoint is the change in MoCA-K score at week 12 from baseline.

Safety endpoints are the adverse events, significant changes in vital signs and physical examination; and abnormal laboratory tests, electrocardiogram, and chest radiography results. Laboratory tests will include hematology, electrolyte, blood chemistry, lipid battery, blood coagulation, and urinalysis.

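### The K-NIHSS 0–2 proportion is compared without adjustment for entry K-NIHSS, which gives up precision (roughly 0 to 15 points of power under assumed inputs) on a secondary endpoint

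*Protocol article*

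**What the plan says.** Under Eligibility criteria (2.2), patients must "have a Korean version of the National Institutes of Health Stroke scale (K-NIHSS) score ≥4 and ≤15 at screening". Under Outcome measures and endpoints (2.6), one secondary endpoint is "the proportion of subjects with a K-NIHSS score of 0 to 2 at week 12", with the same cut for every patient. K-NIHSS is also recorded at baseline and at weeks 4 and 12.

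Under Statistical analysis (2.8), for the responder proportions "a Chi-squared test will be conducted, and if there is an intergroup difference in proportion, a Hochberg test will be carried out" to compare the three arms. The first item on that list is the "intergroup comparison of the proportion of subjects with K-NIHSS score 0 to 2 at week 12". No covariate or severity stratum is named.

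Two other passages bear on this:
- Randomization and blinding (2.5): "Randomization will be stratified according to the hospital, so that all hospitals have a 1:1:1 ratio". Entry severity is not a stratum.
- Statistical analysis (2.8), primary endpoint: "analysis of covariance, with baseline FMA as a covariate, and Tukey multiple comparison test will be carried out". The plan therefore adjusts for baseline where the outcome is FMA change.

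Section 2.8 also analyses change in K-NIHSS from baseline at weeks 4 and 12 by GEE.

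**The concern.** The responder criterion is an absolute end score applied to a wide entry range. The fall a patient needs is fixed by the entry score, so entry score is likely to be a strong predictor of response. A test that ignores a strong predictor leaves explainable variation in the comparison. With about 22 evaluable patients per arm there is little precision to spare, and the needed covariate is already collected. The protocol names the test itself, so an SAP that follows the protocol would carry the unadjusted test forward.

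What is at stake is the power and precision of one secondary comparison in a trial meant to inform dose choice and a later phase 3 trial.

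**Working it through.** **Inputs from the protocol article.** Entry K-NIHSS 4–15 (2.2); responder cut 0–2 (2.6); chi-squared then Hochberg (2.8); two-sided 10% (2.8); difference 14.5, SD 19.2, power 80%, 22 per arm, 15% drop-out, 26 per arm enrolled (2.7).

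**The plan's own figure.** n = 2 × (1.645 + 0.842)² × 19.2² / 14.5² = 21.7, so 22 per arm; 22 / 0.85 = 25.9, so 26. Both reproduce. They concern the primary endpoint. The article gives no power for the K-NIHSS proportion, so 22 per arm is carried over as the evaluable number.

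**Fall needed to reach 2.** From 4: 4 − 2 = 2 points. From 15: 15 − 2 = 13 points.

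**Chance imbalance in entry score (assumed distributions).** If entry score is uniform on 4–15, its SD is √((12² − 1)/12) = 3.45. The standard error of the difference in arm means is 3.45 × √(2/22) = 1.04 points. With entry skewed towards low scores (SD 3.02) it is 0.91. A difference of at least 1 point then arises in about 34% and 27% of pairwise comparisons respectively.

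**What a 1-point imbalance does.** Let the log-odds of response fall by 0.2 to 0.5 per entry point (assumed). A 1-point imbalance then moves the responder proportion by about 4 to 8 percentage points, and by about 6 at slope 0.35. The yardstick is the sampling error of the crude difference: with rates near 50%, √(2 × 0.25/22) = 0.15, or 15 points. A 6-point shift is 6/15 = 0.4 of a standard error, and the crude test's standard error already contains this source of variation.

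**Power, one pairwise comparison, 22 v 22, two-sided 10%.** Simulated with log odds ratio 1.4 and size-correct tests (null rates 9–10%). The figures are the gain from adjusting for entry K-NIHSS.

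| Slope per entry point | Uniform entry | Entry skewed low |
|---|---|---|
| 0 | no loss | no loss |
| 0.2 | about 3 points | about 2 points |
| 0.35 | about 10 points | about 8 points |
| 0.5 | about 15 points | about 12 points |

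With a narrower skewed distribution (SD 2.8) and both tests calibrated to a true 10%, power was 65% v 65%, 52% v 55% and 44% v 51% at slopes 0.2, 0.35 and 0.5: gains of 0, 3 and 7 points.

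**A second alternative.** With marginal response held at 30% v 60% (6,000 runs per setting; adjusted test a linear model on the 0/1 outcome), crude v adjusted power was:
- uniform entry, slopes 0, 0.2, 0.35, 0.5: 64 v 64, 65 v 68, 65 v 74, 64 v 81%;
- skewed-low entry: 65 v 64, 65 v 67, 65 v 70, 64 v 75%.

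The largest gain here is about 17 points. Null rates were 10.5–11.4% for the crude test and 9.4–10.6% for the adjusted test. The crude excess is also present at slope 0 (11.2%), so it reflects small-sample discreteness and not entry severity.

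**The case against.** Nothing here is stated wrongly or contradicted. A chi-squared test of proportions is valid under randomisation, and the choice is one of efficiency on one of four responder comparisons in an exploratory trial whose primary endpoint is already baseline-adjusted. That stands, and it sets the weight of the point.

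A reader might infer two stronger things that the documents do not support:
- **That chance imbalance in severity biases the comparison or produces false positives.** It does not. Imbalance is part of the sampling error that the crude test already allows for; a 6-point shift against a 15-point standard error is not a bias.
- **That a patient who goes from 15 to 3 is lost to the analysis as a failure.** On the 0–2 criterion this patient is a non-responder, but the GEE analysis of K-NIHSS change credits the 12 points. The 0–2 cut asks a different question, namely who ends nearly free of deficit, and there is no reason to abandon it.

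It is also fair to object that the gain rests on inputs absent from the document (entry distribution, slope, odds ratio), that it is for a single pairwise comparison and not the three-arm test with Hochberg, and that a plain likelihood-ratio test would flatter adjustment, since it runs somewhat above 10% under the null at this size. The first two limits stand. The third is met by relying above on tests that hold their size.

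**Conclusion.** The point holds as a low-severity improvement. The plan fixes an unadjusted test for an outcome that entry score is likely to predict, when that score is already collected and not balanced by stratification. The cost is precision. Under the assumed inputs (22 per arm, log odds ratio 1.4, two-sided 10%, one pairwise comparison), adjustment gains roughly 0 to 15 points of power. The low end applies where entry scores cluster low or predict weakly, and the high end where they spread evenly and predict strongly. If entry score does not predict response, the loss is negligible. The primary endpoint and the sample size are unaffected.

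**What to change.** In section 2.8, compare the K-NIHSS 0–2 proportion by logistic regression with arm and entry K-NIHSS as a continuous covariate. Because the arms are small, take the p-value from a penalised likelihood or a permutation test. Report the standardised difference in proportions beside the crude percentages. Keep the 0–2 definition and the Hochberg step for the pairwise comparisons.

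The cost is a wording change and slightly more analysis work. No new data are needed, and the change can be made in the SAP, which section 2.8 says will be finalised before database lock.

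### In the FAS, the week-12 MoCA-K ANCOVA leaves week-4 scores unused; a repeated-measures model would recover a little precision at almost no cost

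*Protocol article*

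**What the plan says.** All references are to the protocol article.

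- **Section 2.6, visits:** K-NIHSS, K-mRS, K-MBI and "the montreal cognitive assessment (MoCA-K) will be used at baseline and weeks 4 and 12".
- **Section 2.6, endpoint:** "Exploratory endpoint is the change in MoCA-K score at week 12 from baseline". Section 1.1 makes cognition the exploratory objective, and MoCA-K is its only measure.
- **Section 2.8, test:** for the exploratory endpoint, "change in MoCA-K score at week 12 from the baseline, analysis of covariance and Tukey multiple comparison test will be carried out". The covariate is not named here; I take it to be baseline MoCA-K.
- **Section 2.8, other scales:** "For the following secondary efficacy endpoints, generalized estimating equation analysis will be conducted for overall data or by subgroup". The list that follows covers K-NIHSS, K-mRS and K-MBI at weeks 4 and 12. MoCA-K is not on it.
- **Section 2.8, missing data:** "the last observation carried forward method will be used for FMA motor score, the primary outcome variable". For the rest: "Similarly, for the other outcome variables, missing data will not be substituted and included in the statistical analysis".
- **Section 2.8, analysis sets:** FAS membership needs one FMA at week 4, 8 or 12. Secondary and exploratory endpoints are analysed in both the FAS and the PP set, "with the final conclusions to be made based on the PP set results".

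**The concern.** Taken together, these statements make the MoCA-K comparison a complete-case analysis at week 12. A patient who leaves after the week-4 visit can be in the FAS, through the week-4 FMA, and can have a week-4 MoCA-K. That patient still adds nothing to the MoCA-K test, and the week-4 score enters no stated between-group analysis.

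Two things follow for the FAS result:

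- **Precision.** The week-4 score predicts the missing week-12 score to some degree, and that information goes unused.
- **Assumption.** Complete-case ANCOVA is safe if week-12 missingness depends only on arm and baseline. A likelihood model that includes week 4 also allows missingness to depend on the observed week-4 score. That is a weaker requirement, met with data the trial already collects.

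This is a stated choice and not a detail left to the analysis plan, because the article fixes the model, the time point and the missing-data rule.

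**Working it through.** **1. The plan's own figure.** There is no sample size for MoCA-K, so the counts come from the primary endpoint in section 2.7: difference 14.5, SD 19.2, two-sided 10% level, power 80%, dropout 15%.

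- n per arm = 2 × 19.2² × (1.645 + 0.842)² / 14.5² = 737.28 × 6.18 / 210.25 ≈ 21.7, so 22.
- 22 / 0.85 = 25.9, so 26 per arm and 78 in total.

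Both figures reproduce. Applying the same 15% to MoCA-K (an assumption), about 22 of 26 per arm have a week-12 score and about 4 do not. Across the trial that is about 66 and 12.

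**2. Does any reading of the missing-data sentence bring week 4 in?** The wording is awkward. Whether it means that missing values are left out, or only that nothing is imputed, a week-12 ANCOVA uses week-12 scores only.

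**3. Gain in the FAS.** Let n12 be the number per arm with a week-12 score, n4 the number with a week-4 score, and ρ the week 4 to week 12 correlation after adjustment for baseline. If everyone with week 12 also has week 4, then:

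- completers only: variance of an arm mean ∝ 1/n12
- likelihood with week 4: variance ∝ (1 − ρ²)/n12 + ρ²/n4
- ratio = 1 − ρ² × (1 − n12/n4)

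With equal arms, the same ratio applies to an arm contrast. The formula treats the regression of week 12 on week 4 as known, so it is slightly optimistic at this sample size. ρ and the timing of losses are not in the document and are assumed.

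| Losses with a week-4 score | n4 | ρ | Variance ratio | Fall in SE | Effective n per arm |
|---|---|---|---|---|---|
| 4 of 4 | 26 | 0.6 | 0.945 | 2.8% | 23.3 |
| 4 of 4 | 26 | 0.7 | 0.925 | 3.8% | 23.8 |
| 4 of 4 | 26 | 0.8 | 0.902 | 5.1% | 24.4 |
| 2 of 4 | 24 | 0.6 | 0.970 | 1.5% | 22.7 |
| 2 of 4 | 24 | 0.7 | 0.959 | 2.1% | 22.9 |
| 2 of 4 | 24 | 0.8 | 0.947 | 2.7% | 23.2 |

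For example, 1 − 0.36 × (1 − 22/26) = 1 − 0.36 × 0.154 = 0.945. A less favourable case, with 1 of 4 losses having week 4 and ρ = 0.5, gives an effective n of 22.2 and an SE only 0.5% smaller.

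**4. Gain in the PP set.** Section 2.8 requires PP patients to have a per-protocol primary efficacy assessment, and the primary endpoint is FMA at week 12. It also excludes overall compliance below 70%. If compliance is counted against the full course, 0.70 × 12 = 8.4 weeks of dosing are needed. Most patients who leave between weeks 4 and 12 are therefore probably outside the PP set. With n4 ≈ n12 the ratio is 1 − ρ² × 0 ≈ 1, which is no material gain.

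**The case against.** The strongest reply is that the plan contains no error here. A prespecified ANCOVA at week 12 is a standard test of an endpoint defined at week 12, and it mirrors the primary analysis. The conclusion rests on the PP set, where the gain is negligible. Even in the FAS, the best case is about 2.4 effective patients per arm, for an exploratory endpoint with no power claim. All of this stands, and it is why the point is of low importance. It does not remove the point, because the FAS analysis is also required and the better use of the data is essentially free.

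A reader might also draw three stronger inferences that the document does not support:

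- **MoCA-K is handled inconsistently with the other scales.** It is not. The K-NIHSS, K-mRS and K-MBI change endpoints are defined at weeks 4 and 12, and the MoCA-K endpoint at week 12 only. The week-12 K-NIHSS and K-mRS proportions are also tested at a single visit.
- **The MoCA-K contrast is biased.** A different early course among leavers is not enough. Dropout would have to depend on the week-4 score beyond baseline and arm, and shift the arms differently. Similar selection in every arm would largely cancel. Nothing in the document indicates the direction or size of any bias.
- **The conclusion loses up to 10% of variance.** That figure is an FAS best case, with every loss after week 4 and ρ = 0.8. It does not describe the PP result.

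**Conclusion.** The point holds as a small, optional improvement. In the FAS, the stated MoCA-K test ignores week-4 scores from patients without a week-12 score. It remains a valid test of its endpoint.

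- **FAS gain:** variance about 3% to 10% lower and standard error about 1.5% to 5% lower. This assumes that the planned 15% loss applies to MoCA-K, that half to all of the losses come after week 4, and that ρ is 0.6 to 0.8.
- **PP gain:** near zero, on the natural reading that most early leavers are already excluded. The PP definition is loosely worded, so a small gain there cannot be ruled out.
- **Primary analysis:** unaffected, including the 22 and 26 per arm.

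**What to change.** In section 2.8, or in the analysis plan before database lock, replace the single-visit MoCA-K ANCOVA with a likelihood-based repeated-measures model for change at weeks 4 and 12. Include arm, visit, arm-by-visit, baseline MoCA-K and baseline-by-visit, with an unstructured covariance. Take the week-12 arm contrasts from it with the planned Tukey adjustment. In the FAS, include every patient with a baseline and at least one post-baseline MoCA-K. The exploratory endpoint stays as defined.

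Two alternatives are weaker. Adding MoCA-K to the generalized estimating equation list would use week 4, but unweighted estimating equations generally need data missing completely at random. Last observation carried forward should not be extended to MoCA-K, since it would treat a week-4 score as a week-12 score.

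The cost is one or two sentences of wording, with no new visits, data or patients.
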